## Abstract

**Background:**

Sedentary behaviour (sitting) is a highly prevalent negative health behaviour, with individuals of all ages exposed to environments that promote prolonged sitting. Excessive sedentary behaviour adversely affects health in children and adults. As sedentary behaviour tracks from childhood into adulthood, the reduction of sedentary time in young people is key for the prevention of chronic diseases that result from excessive sitting in later life. The sedentary school classroom represents an ideal setting for environmental change, through the provision of sit-stand desks. Whilst the use of sit-stand desks in classrooms demonstrates positive effects in some key outcomes, evidence is currently limited by small samples and/or short intervention durations, with few studies adopting randomised controlled trial (RCT) designs. This paper describes the protocol of a pilot cluster RCT of a sit-stand desk intervention in primary school classrooms.

**Methods/Design:**

A two-arm pilot cluster RCT will be conducted in eight primary schools (four intervention, four control) with at least 120 year 5 children (aged 9–10 years). Sit-stand desks will replace six standard desks in the intervention classrooms. Teachers will be encouraged to ensure all pupils are exposed to the sit-stand desks for at least 1 h/day on average using a rotation system. Schools assigned to the control arm will continue with their usual practice, no environmental changes will be made to their classrooms. Measurements will be taken at baseline, before randomisation, and at the end of the schools’ academic year. In this study, the primary outcomes of interest will be school and participant recruitment and attrition, acceptability of the intervention, and acceptability and compliance to the proposed outcome measures (including activPAL-measured school-time and school-day sitting, accelerometer-measured physical activity, adiposity, blood pressure, cognitive function, academic progress, engagement, and behaviour) for inclusion in a definitive trial. A full process evaluation and an exploratory economic evaluation will also be conducted to further inform a definitive trial.

**Discussion:**

The primary output of this study will be acceptability data to inform the development of a definitive cluster RCT designed to examine the efficacy of this intervention on health- and education-related outcomes in UK primary school children.

**Trial registration:**

ISRCTN12915848 (retrospectively registered, date registered 9 November 2016).

**Electronic supplementary material:**

The online version of this article (10.1186/s40814-018-0295-3) contains supplementary material, which is available to authorized users.

## Background

Technological advances and changes to our environment and lifestyle have led to increased time being spent in sedentary behaviours [1]. Sedentary behaviour (sitting, lying, and reclining and expending < 1.5 metabolic equivalents [METs] [2]) is ubiquitous in modern society, with individuals of all ages exposed to environments that promote prolonged periods of sitting. Whilst it is acknowledged that physical activity is beneficial to health, sedentary behaviour has also been shown to adversely affect health. For example, high levels of sedentary behaviour have been independently associated with type 2 diabetes, cardiovascular disease, cancer and premature mortality in adults [3, 4].

Sitting is the most prevalent behaviour exhibited during waking hours in children from the UK, accounting for over 65% of their waking time [5], with some children reportedly sitting for over 10 h/day (> 70% of waking hours) [6]. Adverse associations between sedentary behaviour and cardio-metabolic health risk markers (obesity, blood pressure, cholesterol, insulin) have been reported in children [7, 8]. Given this and as sedentary behaviours track throughout childhood into adolescence and adulthood [9], the reduction of sitting time in young people is pertinent for the primary and secondary prevention of chronic diseases that result from excessive sitting in adulthood [3, 4]. Furthermore, with the emergence of an increased cardio-metabolic health risk profile being observed in the first decade of life in some ethnic groups in the UK (for example, higher levels of fasting insulin and triglycerides have been observed in 9–10-years-old British South Asian children in comparison to white British children) [10], may suggest that these individuals could be more vulnerable to the adverse health effects of excessive sitting time. The early reduction of sedentary behaviour in children in such higher-risk groups could be an important strategy for reducing ethnicity-related health inequalities later in life.

Children are increasingly exposed to environments and social norms that encourage prolonged sitting; for example, because the school classroom is equipped with standard desks and chairs, children are expected to sit throughout most lessons. To counter the detrimental effects of prolonged sitting on children’s health [7], strategies are needed to reverse the trend of increasing levels of sedentary behaviour. A meta-analysis of interventions targeting reductions in children’s sedentary behaviour reported an overall decrease of 18 min/day of sitting and reductions in body mass index (BMI) [11]. Whilst most studies were school-based, sedentary behaviour was targeted via behaviour change strategies within non-school settings (i.e. screen time at home). No included studies employed changes to the classroom environment. Classrooms are conducive to high volumes of sitting, with children typically sitting for longer during school hours than non-school hours [12]. Environmental change within the classroom is therefore an obvious means to target children’s sitting time and may address health inequalities in that this environment is accessible to all children. One such strategy in which environmental change to the classroom can be achieved is through the introduction of sit-stand desks. Unlike traditional classroom desks, sit-stand desks are height adjustable and enable the user to alternate between sitting and standing postures.

Rapid increases in sedentary time have been observed in children aged 11 years and above relative to younger age groups [13, 14]. This trial will target year 5 classrooms, comprising children just below this age (9–10-year-olds), with the goal of reducing the typical rise in sedentary time seen during the transition into adolescence, given sedentary behaviours track from childhood into adolescence and adulthood [9]. Furthermore, evidence suggests that children in year 5 upwards are active participants in their own learning, making them an optimal target for classroom interventions that may facilitate learning [15].

Early-phase studies have demonstrated the feasibility of incorporating sit-stand desks in primary school classrooms over the short term (< 12 weeks) [6, 16, 17]. We have previously observed that sit-stand desks enable pupils (9–10-year-olds) to alternate between sitting and standing, without disruption to teaching, learning or behaviour [6]. International studies have shown sit-stand desks in school classrooms to be effective in increasing energy expenditure [18, 19] and standing and movement [20] during the school day. Other research has shown that sit-stand desks in classrooms lead to improvements in children’s posture and musculoskeletal comfort [21, 22] and levels of academic engagement [23] and achievement [22]. Two studies have assessed the impact on sitting directly, both revealed reductions in children’s daily sitting time of approximately 1 h/day over 4 and 9 weeks follow-up [17, 24]. Recent reviews have concluded that the use of sit-stand desks in school classrooms shows promise; however, the evidence to date is limited to relatively small-scale studies with short intervention periods, and a lack of randomised controlled trials (RCTs) [25, 26]. Furthermore, limited research has examined the impact of this type of intervention on children’s learning and academic achievement [25, 26]. This pilot RCT will build on earlier research by assessing the longer-term acceptability of this low burden environmental intervention in primary schools in the UK, along with the acceptability of a range of health and education-related outcome measures to inform a definitive trial.

### Study aim and objectives

The aim of this study is to undertake a pilot cluster RCT of the introduction of sit-stand desks in primary school classrooms to inform a future fully-powered definitive trial. A definitive trial would examine the impact of the introduction of sit-stand desks over one school year on weekday sitting time (the primary outcome), health and education related outcomes, with sub-group analyses for ethnicity. To inform such a trial, key information needs to be established around school and participant recruitment, acceptability of the intervention and outcome measures, and attrition rates. The objectives of this pilot study are therefore to

1. Establish and refine a recruitment strategy for schools and pupils.

2. Determine attrition in the trial (schools and children).

3. Determine completion rates for outcome measures (and whether these are sufficiently high to provide accurate data in a full trial).

4. Assess whether there are any differences in trial recruitment, retention and acceptability between ethnic groups.

5. Assess the acceptability of randomisation to schools to the intervention or standard practice.

6. Assess the acceptability of measurement instruments to teachers, children and parents, including the activPAL inclinometer as the tool for the measurement of the primary outcome.

7. Assess the acceptability of the intervention to teachers, children and parents.

8. Monitor any adverse effects, such as musculoskeletal discomfort and/or disruption to the classroom environment/teaching and learning to inform the design of a full trial and minimise or eliminate any such effects.

9. Assess intervention fidelity.

10. Derive preliminary estimates of the effect of the intervention on children’s total daily sitting time, physical activity, indicators of health (markers of adiposity and blood pressure), cognitive function, quality of life, and academic performance, engagement and behaviour.

11. Estimate the standard deviation of the primary outcome to inform a sample size calculation for a full RCT.

12. Determine availability and completeness of economic data and conduct a preliminary assessment of potential cost-effectiveness.

## Methods/Design

The design of this study is based on guidance from the UK Medical Research Council for developing and evaluating complex interventions [27]. This is a school-based, pilot two-armed cluster RCT with economic and process evaluations. Individuals (year 5 children, aged 9–10 years) will be the unit of analysis and schools (clusters) randomly assigned to one of two conditions: (1) six manually adjustable sit-stand desks incorporated into the classroom environment (intervention condition), or (2) current practice (control condition). Baseline measurements will precede randomisation. The sit-stand desks will be installed into the intervention classrooms following randomisation. An identical set of outcome measurements will be taken from all participants approximately 6 months after the baseline measures, when participants are at the end of year 5. Observations, interviews and focus groups with teachers, children and parents will be conducted throughout the intervention period as part of a full process evaluation. Figure 1 shows the study flow diagram, and Fig. 2 indicates the schedule of enrolment, intervention and outcome measurements. The project has been granted ethical approval by the Loughborough University Ethical Advisory Committee (reference R16-P027).

**Fig. 1 Fig1:**
[figure not shown]
Flow diagram for the Stand Out in Class pilot RCT

**Fig. 2 Fig2:**
[figure not shown]
Standard Protocol Items: Recommendations for Interventional Trials (SPIRIT) diagram illustrating the design and timescales of the pilot Stand Out in Class RCT

### Setting

This study will be conducted in primary schools in Bradford. Bradford was chosen as the study location given its ethnic composition (predominantly South Asian and White British) and high levels of deprivation, health inequalities and childhood morbidity [28]. In 2016–17, 38% of year 6 children in Bradford were overweight or obese according to the National Child Measurement Programme [29]. Half of all babies born in Bradford are of South Asian origin and 60% are born into the poorest 20% of the population [28], with elevated risk factors for chronic diseases seen in South Asian children in comparison to White children [10, 30]. The setting of this study therefore is fundamental in addressing the important issue of health inequalities, in that the intervention will be accessible to all children. In addition, the location enables us to pilot this intervention under challenging circumstances meaning that if it proves acceptable it is likely to be transferable to most schools.

### Sample size

Eight primary schools, each with at least 15 child participants (approximately 50% of a typical class) will be recruited giving a minimum total sample of 120. This sample matches the minimum of four clusters per arm recommended for a cluster RCT [31], and the minimum sample size exceeds the recommendation for pilot trials [32]. Consequently, the sample will be sufficiently large to provide clear estimates of recruitment and follow-up for a definitive trial.

### School recruitment and inclusion criteria

Government funded primary schools located in the City of Bradford will be invited to participate in the study following ethical approval. Private and designated special schools and schools with less than 25 pupils in year 5 will be excluded. Schools will also not be eligible for participation if they are running a sitting time reduction programme, or if they have a unique characteristic that prevents comparison with control schools. The study will be publicised to primary schools through existing local networks (e.g. Bradford Primary Improvement Partnership and Bradford’s Public Forum for Education). We will aim to recruit four schools with predominantly South Asian pupils (> 50%) and four schools with predominantly White British pupils (> 50%). Interested schools will be followed-up via telephone and visits by the research team. Consent will be sought from school management (Head Teacher, Senior Teachers, Governors) and year 5 teachers to participate in the study. During recruitment, schools will be informed they may be randomised to a current practice control condition where they will be asked to maintain their usual classroom practice.

### Participant recruitment and inclusion criteria

All year 5 children (9–10-years-old) within the participating schools will be eligible to participate. Parents will be sent a detailed information sheet about the study so that they can make an informed decision about their child’s participation. They will also be invited to a school meeting outlining the study. Parental/guardian consent (through an opt-in form for their child to participate in the intervention evaluation) will be collected. Children will be asked to provide verbal assent at each data collection time point for the evaluation measures. Children without parental consent for their participation in the evaluation, or those who do not give their assent to participate in the evaluation, will be excluded from the evaluation measures described below. These children will however be able to use the sit-stand desks within their classrooms. Any children in the intervention schools with known contraindications (for example, a musculoskeletal injury, a wheelchair user) that would preclude periods of standing will be invited to participate in the evaluation measures and encouraged to use the sit-stand desk in a seated posture for inclusivity. These individuals will however be excluded from the analyses.

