### Allocation to treatment groups

To assess the acceptability of the intervention and proposed outcome measures for use in a definitive trial across an ethnically diverse sample, recruited schools will be stratified based on the ethnic composition of their pupils (identified above). Schools within each stratum will be randomised into the two study arms (intervention and control, using an allocation ratio of 1:1) by an independent statistician at the Leicester Clinical Trials Unit (CTU) following the completion of baseline measurements. Two schools with predominantly South Asian pupils and two schools with predominantly White British pupils will be randomised into the intervention and control arms (four schools in each arm). Stratification of schools will enable us to examine whether there are ethnic differences in terms of participant recruitment and retention, adherence to the outcome measures, and preliminary effects of the intervention on outcome measures. The statistician performing the analyses will be blinded to the schools allocation to the study arms, as will the community researchers undertaking the outcome measurements.

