### Control arm

To compare the effects of the intervention against usual practice (i.e. the provision of standard classroom desks), schools assigned to the control arm will be requested to continue with their usual practice and lesson delivery, no environmental changes will be made to their classrooms. The year 5 participants in the control schools will be asked to complete the same study measurements as those in the intervention schools at the same time points. Upon completion of the study, control schools will receive a report summarising their pupils’ sitting and physical activity data. They will also receive adapted materials (i.e. the Professional Development Manual provided to teachers in the intervention schools outlining the benefits of reducing sitting but excluding references to sit-stand desks) upon completion of all follow-up evaluation measures.

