### Data analysis

#### Statistical analysis

This study will be analysed and reported according to the Consolidation Standards of Reporting Trials (CONSORT) statement for cluster RCTs [64]. Data will be analysed on a complete-case basis. The purpose of the primary analysis is to assess the feasibility of recruitment and adherence/retention of primary schools and pupils to a sit-stand desk intervention. As this is a pilot trial, the primary analyses will mainly utilise descriptive statistics. We will summarise the number of schools approached, the number agreeing to participate, the proportion of children within each school with parental consent to participate in the study evaluation, the number of children completing the study protocol, retention rates, and the number providing valid outcome measurement data at baseline and follow-up. The study acceptability data will be presented for the sample as a whole and stratified according to study arm (intervention and control) and ethnicity (South Asian and White British).

While the main aim of this study is to establish acceptability, feasibility, recruitment rates and sample size to inform a definitive trial, and although effectiveness will unlikely be established with the small sample size, we will examine the primary and secondary outcomes to mimic practice for a full trial. Results from this analysis will be treated as preliminary and interpreted with caution [65, 66]. As the number of clusters is low, cluster summary statistics will be used rather than multi-level modelling [67, 68]. The analysis will be carried out using children as the unit of analysis with change in average total school-day sitting time as the primary outcome. A weighted linear regression model will be used to compare the intervention arms weighted by the number of participants followed up in each cluster and adjusted for baseline total daily sitting time on school days for each cluster. To examine preliminary effects of the intervention on the secondary outcomes, the same analytical approach will be adopted as for the primary outcome (objective 10). These analyses will provide preliminary evidence of the effectiveness of the intervention and will in-part inform the decision of whether a definitive trial should be undertaken.

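### Children who cannot stand are dropped from the analyses only if their school is allocated desks, so the two arms are analysed on different populations

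*Protocol article*

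**What the plan says.** Eligibility is open in both arms: every year 5 child "within the participating schools will be eligible to participate" (Protocol article, Participant recruitment and inclusion criteria). The same section then defines a subgroup by arm: "Any children in the intervention schools with known contraindications (for example, a musculoskeletal injury, a wheelchair user) that would preclude periods of standing". These children are invited to be measured and to use the desks seated. The rule that follows is: "These individuals will however be excluded from the analyses". Which analyses are meant is not said.

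The Control arm section contains no counterpart: "The year 5 participants in the control schools will be asked to complete the same study measurements as those in the intervention schools". The timing of measurement is matched too, and no exclusion is mentioned. Allocation to treatment groups says that schools are randomised "using an allocation ratio of 1:1" and "following the completion of baseline measurements". It also says that the statistician doing the analysis will not know which arm each school is in.

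The Statistical analysis section plans a complete-case, cluster-summary regression "with change in average total school-day sitting time as the primary outcome", weighted by the number followed up and "adjusted for baseline total daily sitting time on school days for each cluster". It gives no rule that would remove control children who cannot stand.

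**The concern.** Take two children with the same contraindication, one in each arm. Both are eligible and both are measured. As written, the child in the desk school is dropped and the child in the control school is kept. The rule can be applied only once allocation is known, so it acts as a post-randomisation exclusion in one arm.

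Three things follow.

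- **Comparability.** Randomisation no longer guarantees that the analysed groups are alike, and the contrast estimates neither the effect in all children nor the effect in children able to stand.
- **Timing.** The word *known* carries no date. A musculoskeletal injury that appears after desk installation could take a child out of the intervention arm only, although objective 8 monitors musculoskeletal discomfort as a possible adverse effect.
- **Blinding.** If exclusions occur only in desk schools, the pattern of exclusions can tell the statistician which schools those are.

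The effect estimates are preliminary, but the Statistical analysis section says that they will partly inform whether a definitive trial goes ahead and that the analysis is meant to mimic that trial. A rule that depends on the arm could therefore carry over.

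**Working it through.** **Plan's own figure.** 8 schools x 15 children = 120, as stated under Sample size. The point does not depend on it, but it sets the scale: 60 children per arm, so 1 in 15 is 4 children per arm and 1 in 30 is 2.

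**Inputs.**
- d, true reduction in sitting among children who can stand: 18 min/day (meta-analysis in Background) or about 60 min/day (two sit-stand desk studies in Background).
- p, share who cannot stand: 1/30 or 1/15. Assumed.
- g and u, change over time without desks in children who can and cannot stand: both 0, or g = 20 and u = 0 min/day. Assumed.
- D, excess baseline sitting of children who cannot stand: 0 or 150 min/day. Assumed.
- b, slope of follow-up on baseline for school means: 0.85. Assumed.

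**Formulas** (intervention minus control; negative favours the desks).
- All children kept: -(1 - p)d
- Same exclusion in both arms: -d
- Exclusion in the intervention arm only: -d + p(g - u) - (1 - b)pD

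The second term in the last line arises because control children who cannot stand contribute their own time trend. The third arises because they raise the control baseline, and regression adjustment turns part of that into an apparent effect.

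**Bias of the one-arm exclusion, p = 1/15 (min/day).**

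| g, u, D | Against same exclusion in both arms (any d) | Against all children, d = 18 | Against all children, d = 60 |
|---|---|---|---|
| 0, 0, 0 | 0.0 | -1.2 | -4.0 |
| 0, 0, 150 | -1.5 | -2.7 | -5.5 |
| 20, 0, 0 | +1.3 | +0.1 | -2.7 |
| 20, 0, 150 | -0.2 | -1.4 | -4.2 |

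Worked example, second row with d = 60: the one-arm estimate is -60 - 0.15 x 150/15 = -61.5. With all children kept it is -(14/15) x 60 = -56.0. The difference is -5.5.

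At p = 1/30 every entry halves. Against the same exclusion in both arms the range is +0.7 to -0.8. Against all children it is +0.1 to -1.4 for d = 18 and -1.3 to -2.8 for d = 60.

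**Check by simulation.** The planned weighted regression was simulated with 8 schools of 15 children, an assumed SD of 60 min and ICC of 0.1, and 4,000 runs per scenario. With no true effect and p = 1/15, the one-arm estimate averaged +0.3, -1.5, +1.2 and -0.3 in the order of the table rows (simulation error 0.17), in line with the formula. The sampling SD of the estimate was about 10 to 11 min/day.

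**Contraindications that resolve.** The scenarios above treat inability to stand as lasting. If every affected child has an injury at baseline and has recovered by follow-up, then u = g - D and the bias against the same exclusion in both arms becomes pD - (1 - b)pD = bpD. With p = 1/15, D = 150 and b = 0.85 this is 0.85 x 10 = +8.5 min/day, against the desks. This is an extreme case, but it shows that the sign is not fixed.

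**The case against.** The strongest defence is that the sentence was written with desk use in mind and that the authors meant to treat both arms alike. That may be so, but the wording ties the group to intervention schools. An analysis plan applying the exclusion to both arms would have to depart from the protocol, and control schools would still need to record the contraindication. The defence also notes that this is a mainly descriptive pilot whose effect estimates are to be read with caution, and that few children are likely to be affected. Both points stand and limit the severity.

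Three stronger readings are tempting, and the article does not support them.

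- **That the desk effect is biased in its favour.** This is usually so when the target is the effect in all children, because non-responders are removed from one arm. Against the effect in children able to stand, or with no true effect, the bias can be favourable, nil or unfavourable. Nothing in the article shows how much these children sit.
- **That the bias reaches about 10 min/day.** One can reach this by taking 10 h / 0.70 = 14.3 waking hours, giving a wheelchair user 14.3 x 60 x 0.35 = 300 min more sitting than a peer at 65%, dividing by 15 to get 20 min, and halving for a baseline slope of 0.5. The waking hours come from a high-sitting subset and the 65% from a different source; the slope and the prevalence are assumed. The same inputs with a control child who recovers give 20 - 10 = 10 min/day in the opposite direction.
- **That these pupils leave the retention and completion figures.** The article says only that they are excluded from the analyses and does invite them to be measured. The scope is ambiguous; removal from those counts is not stated.

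**Conclusion.** The rule is wrong as written: it makes inclusion in the analysis depend on the allocated arm, so the arms are compared on different populations. It also leaves room for one-sided loss of children injured after installation and can reveal allocation to the statistician. These consequences follow from the text alone.

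The numerical consequence is probably small and of uncertain direction: about +1.3 to -5.5 min/day across the lasting-contraindication scenarios at prevalences of 1 in 30 to 1 in 15, and further against the desks if many of the injuries resolve. All these values lie below the simulated sampling SD of 10 to 11 min/day. They rest on assumed prevalence, time trends, baseline excess and slope, none of which the article gives. The point should be corrected, but it does not invalidate the pilot's recruitment, retention and acceptability results.

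**What to change.** Record contraindications to standing at baseline, before randomisation, in all eight schools, and replace the arm-specific sentence with one rule for both arms. Either of two choices restores comparability:

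- exclude children with a baseline-recorded contraindication from the outcome analyses in both arms, which targets the effect in children able to stand; or
- keep all consented children in the main outcome analysis, with the same two-arm exclusion as a sensitivity analysis, which targets the effect in whole classes.

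The choice depends on the question that the definitive trial will ask, and the protocol should name it. Under either choice, contraindications that arise after randomisation should not lead to exclusion. The text should also say that any exclusion covers only the outcome-effect analyses and leaves the recruitment, retention, completion and adverse-effect summaries intact.

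The cost is one baseline item in all schools and one corrected sentence. Clinical handling and desk use are unchanged.
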